### Target population

The target population will consist of maltreated children aged between 6 and 18 years and their primary caretaker. Inclusion criteria are (1) a report to an AMK about physical and/or emotional abuse, physical and/or emotional neglect and/or sexual abuse, (2) one child per family. When a report relates to more than one child of the same family, the oldest child within the age range will be included, (3) sufficient verbal and cognitive capacities of both parent and child, as the study will use mainly self-report methods for data collection, and (4) no intention to leave the Netherlands within the next 6 months, in view of the follow-up period.

### Sample size and recruitment

Participants from an ongoing prospective study on the mental health and quality of life of maltreated children after a report to an AMK [35] will be contacted to complete assessments A and B (see Figure 1). Parents and children will be asked to give written informed consent for their participation. Five dyads from the sample of this prospective study were excluded because they did not meet age criteria, while for 22 parent–child dyads maltreatment was not verified during the AMK investigation and for 17 dyads the type of maltreatment did not meet inclusion criteria of the quasi-experiment. Hence, the study sample for the present quasi-experiment will include 117 parent–child dyads. A sample size calculation confirmed that this is a sufficient number of participants. Based on the ability to detect a medium effect size or larger clinical effect (Cohen’s d > 0.45) [37] and tested at a conventional power of (1-beta) 0.80 and alpha of 0.05 (one-tailed testing), a total number of 110 parent–child dyads is required.

Supported by AMK records, this sample will be split up into two groups: an intervention group, in which the Child-Interview intervention was used during the AMK investigation, and a control group, in which the intervention was not used (adult-only intervention).

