Over the last decades the focus of the AMK investigations has changed from an adult-only approach to a more child-oriented approach using a Child-Interview intervention. In the adult-only intervention, only adults, including parents, teachers and general practitioners, are asked to provide information to substantiate the alleged abuse. Children are not used as informants in this intervention, for two reasons: the belief that children could not provide reliable and accurate information and the belief that children should not be troubled with questions about maltreatment. Regarding the first reason, several studies have shown that children can be reliable informants [14-17]. The Child-Interview intervention includes children aged 6 years and over as informants in the AMK investigation, in addition to adult informants. The children are interviewed by an AMK employee. Just as in the adult-only intervention, the aim of this interview is to collect information on the alleged child maltreatment, the existence of any family problems, the child’s needs for help and/or protection and the willingness to accept help and/or protection. An additional aim is to increase the child’s sense of being in control. AMK workers have confirmed the value and relevance of this information provided by children. In their experience, the maltreated children can provide highly relevant information that is otherwise not retrieved and this Child-Interview intervention therefore results in potentially better tailored interventions.

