Regarding the second reason, several studies have shown positive effects on the children of talking about their maltreatment experiences. These studies showed that talking about such experiences may be the start of the recovery process and may increase children’s feelings of control and self-esteem [18-20], whereas keeping maltreatment experiences a secret is associated with additional trauma [21,22]. These findings suggest that the Child-Interview intervention is not only helpful for the referral to well-tailored care, but there are also benefits for the mental health and quality of life of these maltreated children. Nowadays all AMKs in the Netherlands have adopted the Child-Interview intervention and this is the preferred method according to the AMK manual [13]. Nevertheless, AMK records show that the adult-only intervention is still used in many AMK investigations. Little research has been done on the effects of specific AMK interventions [23], and scientific evidence on the presumed superiority of this Child-Interview intervention in comparison to an adult-only intervention is lacking.

In addition, it is well documented that children who have been abused or neglected are more likely to experience adverse outcomes in a number of domains throughout their lives. This results in an increasing demand on multiple services, including healthcare, by both children and their families [23]. Studies in the US have shown that substantial costs are associated with the impact of child maltreatment [24,25]. In the Netherlands, Meerding [26] estimated the economic burden of child maltreatment to be 965 million euros in 2003, which is about 138 euros per household annually. This was probably an underestimation, however, because the prevalence of child maltreatment in the Netherlands had not been studied yet and the estimates used were much lower than the recent prevalence rates reported by Alink and colleagues [10].

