## Discussion

The value of having children participate in the AMK investigations by using the Child-Interview intervention is increasingly being recognized. The intervention yields valuable information to substantiate the alleged maltreatment report, and the intervention is also expected to be beneficial for the mental health and quality of life of the maltreated children. However, this beneficial effect has not yet been studied. In addition, child maltreatment is associated with substantial societal costs because of the high demand for healthcare and other services by both the maltreated children and their families. Using the Child-Interview intervention may prevent or reduce negative outcomes of child maltreatment, which may result in a lower consumption of healthcare and other services.

Although the AMK manual suggests that using the Child-Interview intervention during AMK investigation is the preferred method, the AMKs in the Netherlands are still in a transition period as regards the nature of the investigation. From a small survey among AMKs we estimate that the adult-only intervention is still used in approximately 40% of all investigations by the AMKs. At this point in time, this enables us to answer the research questions by means of the proposed quasi-experimental design, before the Child-Interview intervention is fully adopted, as the percentage of cases in which the intervention is not used is still sufficient. We will be able to derive two study groups with acceptable sample sizes from an ongoing study examining the mental health and quality of life of children reported as being maltreated.

A strong point of the proposed study is the use of child self-reports to collect data on quality of life, one of the main outcome measures of the effectiveness study. Data on quality of life are often collected using proxies, but research findings show discrepancies between child and proxy reports [43]. As a consequence, the value of obtaining children’s self-reports is increasingly recognized and several studies have established the accuracy and reliability of child reports [39,43-45].

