Another limitation is the possible recall bias caused by the time that elapses between the assessment moments. A period of 3 months is generally used between assessments in economic evaluations. However, this study will use a period of 6 months because the assessment moments will be connected to those of the ongoing prospective study. Respondents may have difficulty remembering the exact number of times they used healthcare and other services, which may affect outcomes.

To conclude, within the constraints of ethical and legal standards, the quasi-experimental study design we chose is expected to provide information on the optimal approach for AMK investigation, in terms of effectiveness and cost-effectiveness. The aim of an AMK investigation is to refer the child and family to well-tailored care and to end substantiated maltreatment. The use of the Child-Interview intervention may contribute to the prevention of negative outcomes of child maltreatment, if using this intervention during the AMK investigation proves to result in better mental health and quality of life outcomes for maltreated children because well-tailored care can be provided on the basis of information that cannot be retrieved with the adult-only intervention. Policy makers are increasingly interested in the cost-effectiveness of methods being used, and cost-effectiveness studies are increasingly used in the development of new policies.

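### The sample size rests on an unjustified one-tailed test at 0.05, although the protocol calls superiority unproven and asks which approach is optimal; 117 dyads look sufficient partly because of that choice

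*Protocol article*

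**What the plan says.** Sidedness appears once, in the Protocol article under Sample size and recruitment. The target there is set by "Based on the ability to detect a medium effect size or larger clinical effect (Cohen’s d > 0.45", "tested at a conventional power of (1-beta) 0.80 and alpha of 0.05 (one-tailed testing", and the result is that "a total number of 110 parent–child dyads is required". The same section says that "the study sample for the present quasi-experiment will include 117 parent–child dyads" and calls this number sufficient. It gives no reason for a one-tailed test and does not name the tail.

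Under Analyses, the effectiveness subsection says only that mental health and quality of life will be compared between the groups by multivariate regression. It fixes no sidedness and no direction.

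The rest of the article bears on the choice in two ways:

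- The Background presumes superiority and the Discussion expects benefit, so the implied tail is benefit.
- The Background also says that "scientific evidence on the presumed superiority of this Child-Interview intervention in comparison to an adult-only intervention is lacking". The primary aim is neutral (to examine the effect of participation), and the Discussion says the design "is expected to provide information on the optimal approach for AMK investigation".

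**The concern.** A one-tailed test is reasonable when a result in the other direction is not credible, or would lead to the same action as no difference. The article does not argue either, and its own statements point the other way. Superiority is described as unproven, and choosing between two approaches calls for a test that can favour either one.

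The Child-Interview is already the preferred method in the AMK manual. A finding of no demonstrated benefit and a finding of worse outcomes would therefore mean different things for practice, and a test for benefit alone does not separate them.

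The second consequence concerns the sample size. At a given effect, a one-tailed 0.05 test needs fewer participants than a two-sided one, so the statement that 117 dyads suffice depends partly on this choice.

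**Working it through.** **Inputs.** From Sample size and recruitment: d = 0.45 (the stated threshold, with SD = 1 on that scale), alpha 0.05, power 0.80, 110 dyads required, 117 available. The group split is not stated there. The Discussion estimates that "the adult-only intervention is still used in approximately 40% of all investigations by the AMKs", so I tried equal groups and 60:40. The 60:40 split is an assumption about this sample.

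**1. The plan's own figure, one-tailed, equal groups.**

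n per group = 2 × (z₁₋α + z₁₋β)² / d²
= 2 × (1.645 + 0.842)² / 0.45²
= 2 × 6.183 / 0.2025 = 61.1, rounded up to 62, so 124 in total.

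The noncentral t calculation gives 61.7 per group, also 124. At 60:40 the total is 128 (normal) or 129 (t). The stated 110 is not reproduced. It does appear with d of about 0.475 (normal) or 0.48 (t), or with covariate adjustment at a correlation of about 0.35. The article states neither.

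**2. The same target, two-sided.**

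n per group = 2 × (1.960 + 0.842)² / 0.45² = 2 × 7.849 / 0.2025 = 77.5, rounded up to 78, so 156 in total.

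By noncentral t it is 158. At 60:40 it is 163 (normal) or about 164 (t). The 117 available dyads are 39 (156 − 117) to 47 (164 − 117) short.

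**3. What 117 dyads deliver (noncentral t).**

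| Split | Test | Power at d = 0.45 | Detectable d at 80% power |
|---|---|---|---|
| Equal | one-tailed | 0.78 | 0.46 |
| Equal | two-sided | 0.67 | 0.52 |
| 60:40 | one-tailed | 0.77 | 0.47 |
| 60:40 | two-sided | 0.66 | 0.53 |

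**4. An adverse difference of the same size.** Take 70 and 47 dyads and a true d of −0.45, a hypothetical value.

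Standard error = √(1/70 + 1/47) = 0.1886.
Shift = 0.45 / 0.1886 = 2.39 standard errors.

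The one-tailed test for benefit rejects with probability of about 0.00003, and any such rejection would point to benefit. A two-sided test finds the adverse difference with probability of about 0.66.

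**The case against.** The strongest reply is that the one-tailed statement belongs to the sample size calculation, while the analysis section leaves sidedness open. Sidedness and interval reporting are often settled in an analysis plan, which is not at hand. This stands. A reader might infer that the final test is fixed as one-tailed for benefit and that the study cannot conclude otherwise, but the article does not establish that. The direction, too, is implied and not written.

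A reader might also infer that the protocol itself names harm from the interview as a risk. It does not. The Background reports "the belief that children should not be troubled with questions about maltreatment" as one of two reasons behind the adult-only approach, then answers it with studies showing positive effects of talking. The Discussion mentions additional strain only for a child already seen by a therapist or social worker, as one reason a team may choose the adult-only route.

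Nor is the significance test the only place where an unfavourable result could show. The cost-effectiveness plane plots bootstrapped differences in effect, negative ones included. An argument from missing safety oversight or stopping rules has no force, because the study assigns no intervention and only follows up dyads already investigated.

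Finally, the groups were formed by team choice, and the Discussion concedes that they may differ at baseline. A significant adverse difference would be an association and not proof that interviewing harms children.

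None of this justifies the one-tailed alpha. If a two-sided analysis is intended after all, the power statement does not describe it and still needs correcting.

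**Conclusion.** The point holds in limited form. The only sidedness in the article is one-tailed at 0.05. It is unjustified and fits poorly with unproven superiority, a neutral aim and a promise to inform the choice of approach. If the analysis follows it with the tail towards benefit, a worse outcome after the Child-Interview could not be declared statistically significant.

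The sufficiency claim leans on the same choice. A two-sided test costs about 0.11 of power at d = 0.45 (0.78 to 0.67 with equal groups, 0.77 to 0.66 at 60:40). Even one-tailed, 117 dyads fall below the stated 0.80, and the figure of 110 does not follow from the stated inputs.

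These figures assume a plain two-group comparison of means at exactly d = 0.45, no loss of information from missing data, and one of the two splits. Covariate adjustment could change the power in practice, but the article gives no figure for it. The correction should be made, and it does not call the design into question.

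**What to change.** Under Sample size and recruitment and in the effectiveness analysis:

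- State two-sided testing at 0.05, with two-sided 95% confidence intervals for the CBCL and PedsQL group differences.
- Say that an interval lying wholly on the unfavourable side will be reported as an adverse association, subject to confounding.
- Keep the 117 dyads. Replace the requirement of 110 and the statement of sufficiency with the effect detectable at 80% power: about d = 0.52 with equal groups to 0.53 at 60:40. Give the two-sided power at d = 0.45 as about 0.66 to 0.67. Recompute both once the actual split is known from the AMK records.

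Changing only the word for sidedness would not be enough, because the 110 and the sufficiency statement would then contradict the stated test.

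The cost is wording and a short recalculation, with no new participants or data. The drawback is a less favourable stated detectable effect and an open admission that power at d = 0.45 is below 0.80.

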### Analyses

Data will be analyzed according to the intention-to-treat principle. The similarity of baseline characteristics (socio-demographic characteristics, costs and outcomes) between the two AMK investigation interventions will be examined using univariate tests and Chi-square tests. Loss-to-follow up will be accounted for by imputing missing data using regression imputation.

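### The stated requirement of 110 dyads does not follow from its own inputs: 124 are needed at 1:1, so the calculation does not confirm that 117 is sufficient at d = 0.45

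*Protocol article*

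**What the plan says.** The section on sample size and recruitment in the protocol article gives a complete calculation. The target effect is set out as follows: "Based on the ability to detect a medium effect size or larger clinical effect (Cohen’s d > 0.45"). The comparison is "tested at a conventional power of (1-beta) 0.80", and at an "alpha of 0.05 (one-tailed testing), a total number of 110 parent–child dyads is required".

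The same section arrives at the available sample by exclusions from an ongoing prospective cohort: "the study sample for the present quasi-experiment will include 117 parent–child dyads". It then draws the conclusion: "A sample size calculation confirmed that this is a sufficient number of participants".

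The section gives no group ratio, covariate gain or allowance for loss as part of the calculation. The groups are to be read from the agency's records. Two other places bear on the point. The Discussion reports, from a small survey of the reporting centres, that "the adult-only intervention is still used in approximately 40% of all investigations by the AMKs". The Analyses section says: "Loss-to-follow up will be accounted for by imputing missing data using regression imputation".

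**The concern.** Effect size, power, alpha and sidedness are all printed, so the requirement can be recomputed directly, and the answer is larger than 110. The available 117 lies between the printed requirement and the recomputed one. Correcting the figure therefore also removes the support for calling 117 sufficient at the effect size named.

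The sample is fixed by the parent study and cannot easily be enlarged. This calculation is the only statement in the article from which a reader can judge what the comparison can detect, so it should be accurate.

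**Working it through.** **Inputs, all from the sample size section:** two independent groups, standardised difference d = 0.45 (the lower bound of the stated range), power 0.80, one-tailed alpha 0.05. The normal quantiles are 1.645 and 0.842, and (1.645 + 0.842)² is about 6.183.

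**Step 1: try to reproduce 110 at 1:1.**
- Normal approximation: n per group = 2 × 6.183 / 0.45² = 61.06, rounded up to 62, so 124 in total.
- Exact noncentral t: 61:61 gives power 0.796 and 62:62 gives 0.801, so again 124.
- The stated 110 is 14 dyads short (14/124 = 11%), too much for rounding.

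**Step 2: look for a variant that gives 110.**
- Two-tailed testing moves away from it: 156 by the normal approximation.
- Any unequal split also raises the requirement.
- 110 is reached if d is about 0.475 (normal) or 0.48 (exact t), or if power is about 0.76.
- 110 is also reached if covariates explain a share R² of outcome variance with 124 × (1 − R²) = 110, so R² = 1 − 110/124 = 0.11.
- The article states none of these.

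**Step 3: power at d = 0.45, one-tailed 0.05, 1:1.** With N in total, the normal approximation is Φ(d√(N/4) − 1.645).
- N = 110: 0.45 × √27.5 = 2.360, and Φ(0.715) = 0.763. Exact t: 0.758.
- N = 117: 0.45 × √29.25 = 2.434, and Φ(0.789) = 0.785. Exact t: 0.781.

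**Step 4: effect detectable with 80% power at 1:1 (exact t).**
- N = 110: d = 0.477.
- N = 117: d = 0.462.

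**Step 5: illustration only, if this sample had the surveyed 40% adult-only share.**
- Requirement: 6.183 / (0.6 × 0.4 × 0.45²) = 6.183 / 0.0486 = 127.2 by the normal approximation. Exact t: 129 (77:52).
- 117 dyads give power 0.766, and reach 80% at d = 0.472.

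**Step 6: sensitivity to loss.** The article gives no rate, so these are assumptions. At 1:1 and d = 0.45, losing 5%, 10% or 20% of the 117 leaves power of about 0.76, 0.74 or 0.70.

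**The case against.** The strongest reply is that the shortfall is too small to matter. The article names a threshold with an inequality, d greater than 0.45, and 117 dyads reach 80% power at about 0.46. At d = 0.50 they give about 85% power at 1:1 and 84% at 60:40. This stands as a limit on the size of the point. It does not rescue the figure of 110, because 0.45 is the value offered as the basis of the calculation, and effects just above it also have less than 80% power.

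A second reply is that the planned analysis is a regression with covariates, which can reduce residual variance. If covariates explained an assumed 10% of outcome variance, 117 dyads would have 81.7% power at 1:1 and 80.4% at 60:40. That is possible, but the article claims no such gain. A reader might infer the reverse, that adjusting for confounders must lower power further. The documents do not support that either: they give neither the outcome variance explained nor the association of covariates with group, so the net direction is unknown.

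A third reply concerns the split. A reader might take 60:40 as the plan's own ratio and 129 as the true requirement. The 40% is a survey estimate for all investigations by these centres. The 117 are a recruited subset after exclusions, and their split is not stated. So 129 is an illustration, and the error is established at 1:1 without it.

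Finally, the lack of an attrition allowance is not itself an error here, since a condensed article may leave it to the full protocol.

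**Conclusion.** The point holds as a correction of a stated figure. From the printed inputs, 124 dyads are required at 1:1 and not 110, and the calculation does not confirm that 117 is sufficient at d = 0.45. Power at that effect is about 76% with 110 and about 78% with 117. The latter is about 2 points below target at 1:1, and about 3 points below if the surveyed share happened to apply, in both cases before refusal or loss.

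This rests on an unadjusted comparison of two independent means at the lower bound of the stated effect range. A reader might go further and conclude that the study is seriously underpowered, or that a null result could say nothing about a medium effect. The figures do not support that: the detectable effect moves by only 0.01 to 0.02, and power at d = 0.50 is about 84 to 85% before loss.

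**What to change.** In the sample size section:
- Replace 110 with 124, stating that it assumes equal groups and includes no allowance for loss.
- Replace the sufficiency statement with what the 117 dyads provide at 1:1 before loss to follow-up: about 78% power at d = 0.45, or 80% power at d of about 0.46.
- If helpful, add as a labelled illustration that at a 60:40 split the requirement would be about 129, and 117 would give about 77% power (80% at d of about 0.47). Once the split is known from the records, use the actual group sizes.
- If 110 was obtained by assuming a covariate gain (R-squared of about 0.11), state that assumption and its source instead.

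The cost is wording only. No participants are added and neither the design nor the analysis changes; the stated power becomes slightly less favourable.
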